#### Patient data

The following patient data are extracted from the medical records: age, gender, APACHE II (Acute Physiology and Chronic Health evaluation, score 0–74), SAPS II (Simplified Acute Physiology Score, scores varying from 0 to 163 and a predicted mortality rate between 0 and 100%)), reason for the ICU admission, deceased during the ICU stay, length of ICU stay, specialty of referring physician, surgical patient or non-surgical patient, ward from which the patient was referred to the ICU [emergency room (ER), general ward, OR, cardiac care unit (CCU), home] and type of admission [planned, emergency, organ transplantation]. Both APACHE II and SAPS II are general illness severity scores, APACHE is the world most widely applied severity of illness score, whereas SAPS is developed in France and validated in 12 European/North American countries. Both scores are based on the worst values recorded in the first 24 h of the ICU stay and are used in the ICU to predict outcome. They characterize disease severity and degree of organ dysfunction [25].

#### Medication data

The following information is collected for all medication on the BPMH and/or BPML-GW-24: name of medicine, dose form, medication group, dose and frequency.

We will register for every BPMH medication whether it is (1) prescribed in the PDMS within 24 h after admission, (2) registered in the PDMS as “pre-admission medication”, (3) prescribed pre-ICU in CPOE/CDS and (4) registered as “admission medication” in the ICU discharge letter.

We will register for every BPML-GW24 medication whether it is (1) prescribed in the CPOE/CDS within 24 h after the ICU discharge, (2) in use at discharge on the ICU according tot the PDMS medication chart, (3) noted on the PDMS discharge letter as “ICU medication”.

All discrepancies are scored as intended or non-intended and finally the discrepancy type: omission, start, stop, different dose, substitution or incorrect prescribing will be scored.

#### Intervention program data

During the post-intervention phase the process of medication reconciliation is qualified as A, B or C. Quality A is defined as an optimal reconciliation based on a recent, reliable community pharmacy medication list and a reliable verification with patient and/or his representative. Quality B is defined as an intermediate reconciliation; the pharmacy record is recent and reliable and screened for obvious errors, verification with patient or relative is however not reliable. And finally quality C is defined as a sub-optimal reconciliation with either the community pharmacy medication list lacking or the patient/representative verification lacking.

Other data collected on medication reconciliation are: date of reconciliation, within 24 h of the ICU stay or not, verification with patient and/or representative, time spent on verification (patient’s interview), the total reconciliation time and finally the number of medications on the BPMH and BPML-GW24.

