**Methods:**

This prospective 8-month observational study with a pre- and post-design will assess the effects of the TIM program compared with usual care in two Dutch hospitals. Patients will be included if they are using at least one drug before hospital admission and will stay in the ICU for at least 24 h. They are excluded if they are transferred to another hospital, admitted and discharged in the same weekend or unable to communicate in Dutch or English.

In the TIM program, a clinical pharmacist reconciles patient’s medication history within 24 h after ICU admission, resulting in a “best possible” medication history and presents it to the ICU doctor. At ICU discharge the clinical pharmacist reconciles the prescribed ICU medication and the medication history with the ICU doctor, resulting in an ICU discharge medication list with medication prescription recommendations for the general ward doctor. Primary outcome measures are the proportions of patients with one or more medication transfer errors 24 h after ICU admission and 24 h after ICU discharge. Secondary outcome measures are the proportion of patients with potential adverse drug events, the severity of potential adverse drug events and the associated costs.

For the primary outcome relative risks and 95% confidence intervals will be calculated.

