#### ICU admission

The gold standard is defined as the Best Possible Medication History (BPMH), which includes name, dosage, frequency, and route of all medication taken by a particular patient. The BPMH is created as follows: a pre-admission medication list is collected from the community pharmacy, which is combined with other available information about the patient’s medication, such as a letter from the Emergency department (if applicable), medication used in the general ward or medication lists from the operating room (OR) (if applicable). This medication list is verified by means of an interview with the patient and/or a relative, which will result in a BPMH.

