### Collection of medication lists

#### Pre-intervention phase

For each included patient discharged from the ICU for at least 24 h, a pharmacist generates a BPMH and a BPML-GW-24 in order to trace medication transfer errors.

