#### Post-intervention phase

The pharmacist generates a BPMH for patients newly admitted to the ICU and the Best Possible ICU Medication Discharge List (BPMDL-ICU) for patients planned to be discharged. One day past ICU discharge, a medication chart of current medication in the CPOE/CDS will be printed and a BPML-GW24 will be compiled.

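### The reference medication history is compiled after ICU discharge in the pre-phase but at ICU admission in the post-phase, and graded for quality only in the post-phase, so the two phases may be scored against references of different completeness

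*Protocol article*

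**What the plan says.** Under *The gold standard medication lists*, one procedure defines the BPMH for both phases. A community pharmacy list is combined with other available records, and then: "This medication list is verified by means of an interview with the patient and/or a relative, which will result in a BPMH".

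The timing differs by phase (*Collection of medication lists*):

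- Pre-intervention: "For each included patient discharged from the ICU for at least 24 h, a pharmacist generates a BPMH and a BPML-GW-24".
- Post-intervention: "The pharmacist generates a BPMH for patients newly admitted to the ICU". The abstract adds the target: "a clinical pharmacist reconciles patient’s medication history within 24 h after ICU admission".

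Under *Outcome measures*, an admission MTE is an unintentional departure of the ICU prescriptions from the BPMH. The discharge reference, the BPML-GW24, is built partly from the BPMH and partly from ICU records, the ward prescribing system and, where needed, the ward doctor.

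Under *Intervention program data*: "During the post-intervention phase the process of medication reconciliation is qualified as A, B or C". Grade B means that verification was not reliable. Grade C is a "sub-optimal reconciliation with either the community pharmacy medication list lacking or the patient/representative verification lacking". The same section then lists "date of reconciliation, within 24 h of the ICU stay or not, verification with patient and/or representative". Only the grading sentence is expressly limited to the post-phase. That date and source are also post-phase items is the natural reading of the section heading, but it is not stated.

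**The concern.** The BPMH is the measuring instrument for one primary outcome and an ingredient of the other. It depends on an interview, and the interview takes place at a different clinical moment in each phase: after recovery from the ICU stay in one, near the start of critical illness in the other. The protocol itself foresees that the result will vary in quality, since it defines grades for unreliable or missing verification, yet it plans to grade one phase only.

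A home drug absent from the BPMH cannot be scored as omitted at admission. In the post-phase the same list is also the intervention, because it is entered in the record and shown to the ICU doctor. A drug missing from it is therefore neither corrected nor counted. If the post-phase list is less complete, the MTE proportion falls without any effect of TIM. If the pre-phase list is less complete, a real benefit is understated. The planned logistic regression cannot adjust for a grade that exists in one phase only, and the limitations in the *Discussion* do not raise the point.

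**Working it through.** **The plan's own figure first.** *Sample size* gives 133 per phase for 30% versus 15%, alpha 0.05 and power 0.80.

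- Two-sided, without continuity correction: n = [1.960·√(2·0.225·0.775) + 0.842·√(0.30·0.70 + 0.15·0.85)]² / 0.15² = 120.5, so 121.
- With continuity correction: (120.5/4)·[1 + √(1 + 4/(120.5·0.15))]² = 133.5, so 134 when rounded up. The stated 133 is reproduced within rounding.
- Inflation for 35% mortality: 133/0.65 = 204.6, so 205, as stated.

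This point disputes neither figure. They supply the 30% baseline and the sample sizes used below.

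**The two phases side by side**

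| | Pre-phase | Post-phase |
|---|---|---|
| When the BPMH is compiled | at least 24 h after ICU discharge | at ICU admission, 24 h target |
| Sources | pharmacy list, records, patient and/or relative | the same |
| A/B/C grade | not planned | planned |
| List also shown to the ICU doctor | no | yes |
| BPMH drugs registered (*Medication data*) | yes | yes |

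**Size of a possible artefact.** Assumptions: 30% of patients truly have at least one MTE in both phases (no effect of TIM), errors per patient follow a Poisson distribution, the pre-phase BPMH is complete, and the post-phase BPMH misses a share m of the error-bearing drugs. The documents give no value for m.

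Apparent post-phase proportion = 1 − (1 − 0.30)^(1−m); apparent RR = that proportion / 0.30.

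- m = 0.1: 1 − 0.7^0.9 = 27.5%, RR 0.92
- m = 0.2: 1 − 0.7^0.8 = 24.8%, RR 0.83
- m = 0.3: 1 − 0.7^0.7 = 22.1%, RR 0.74

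Reversing the assumption, so that the pre-phase list misses the same share and the post-phase list is complete, inverts the ratios: 30/27.5 = 1.09, 30/24.8 = 1.21 and 30/22.1 = 1.36.

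**Chance of a falsely significant reduction** (two-sided pooled two-proportion z-test at 0.05, so nominally 2.5% in that direction), when the post-phase list is the less complete one:

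| m | 133 per phase | 205 per phase | about 404 per phase |
|---|---|---|---|
| 0.1 | 7% | 8% | 12% |
| 0.2 | 16% | 22% | 38% |
| 0.3 | 31% | 45% | 73% |

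The figure of 404 is the accrual over 14 weeks that the protocol's own rates imply: 1500/52 × 0.70 × 0.65 × 14 = 184 at one hospital and 1800/52 × 0.70 × 0.65 × 14 = 220 at the other. Doubling the recruitment period does not protect against this error; it makes a false finding more likely.

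**How far it would have to go.** To imitate the whole planned fall from 30% to 15%, the share still detected would be ln(0.85)/ln(0.70) = 0.456, so about 54% of error-bearing drugs would have to be missed. That is well beyond the range above.

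**The case against.** A reader might infer three stronger things. The documents do not support them.

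*The bias favours TIM on both primary outcomes.* No section says that post-phase interviews fail more often or that pre-phase patients answer better. Relatives may be interviewed in both phases. A late pre-phase history may suffer from recall or from lost contact with relatives. An incomplete list can also create discrepancies, because an unlisted home drug that is prescribed may look like an unintended start, which is one of the scored types. The direction is therefore open. For the discharge outcome the link is weaker still: the BPML-GW24 is compiled after ICU discharge in both phases and draws on several sources besides the BPMH.

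*Nothing in the pre-phase allows a check.* *Medication data* registers every BPMH drug, with group, dose and frequency, without limiting this to a phase. Drugs per BPMH can be compared. This tests completeness in part; it says nothing about reliability or source.

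*Every post-phase history is taken in the first 24 h.* The 24 h is a target, recorded as met or not. The program does not run at weekends. A patient admitted just after Friday 17:00 who stays past Monday 8:30 is eligible and might first be seen about 63 h later.

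It is also fair to say that the share missed is assumed, and that sensitivity analyses usually belong in an analysis plan that is not shown. What remains rests on explicit text: different timing, and grading in one phase only.

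**Conclusion.** The point holds in this form: a primary outcome is compared between phases against reference lists made at different clinical moments, and their reliability is graded in only one phase. The result can be biased either way. In the direction that favours TIM, and mainly for the admission outcome, an ineffective program would show an RR of about 0.92 to 0.74 if the post-phase BPMH missed 10% to 30% of error-bearing drugs. This rests on that assumed share, a complete pre-phase list, a true 30% in both phases and Poisson errors. The documents do not show that such a loss occurs, and within this range it could not by itself produce the full planned halving. It is a cheap improvement worth making, not a fatal defect.

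**What to change.** 1. Under *Intervention program data*, record the A/B/C grade, the BPMH date and the source of verification (patient, relative, none) for every BPMH in both phases.
2. Report the grade distribution and the number of drugs per BPMH by phase.
3. Score admission MTEs in both phases against a BPMH with the same information cut-off. In the post-phase, update the BPMH used for scoring with information that emerges before the BPML-GW24 is compiled, and keep the list as presented to the ICU doctor as the record of the intervention. Patients who die on the ICU never reach that cut-off, so state how they are scored.
4. Present grade-stratified results only as a sensitivity analysis. Grade depends on when the interview takes place, so grade A may select different kinds of patient in each phase; restriction to or adjustment for grade can itself introduce bias.

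The cost is a few extra CRF fields, completed by the pharmacist who already compiles the list, the work of updating the scoring list, and some loss of precision in the sensitivity analysis.

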### Data analysis

#### Sample size

The primary outcome of this study is the proportion of patients with one or more transfer errors at admission to the ICU and at discharge from the ICU.

Based on literature the expected proportion of patients with medication errors due to transfer between wards within one hospital is 62% [18]. Based on a conservative interpretation of this study, it was estimated that this proportion is 30% in our study. With an estimated 50% reduction of errors due to the intervention, an alpha of 0.05 and a power of 0.80 the calculated sample size is 133. This sample size is based on patients being alive at discharge for both the pre-intervention as the post-intervention phase.

With an estimated mortality of 35%, in each measurement phase 205 patients should be included. Based on 1500 (Haga Teaching Hospital) and 1800 (Erasmus MC) admissions a year, an estimated loss of 30% due to the ICU stay less than 24 h and another 35% loss due to weekend ICU stay, we estimate a study period of 7 weeks for Erasmus MC and 8 weeks for Haga. To be on the safe side and to measure during a robust intervention period, we will double the number of calculated weeks. Therefore a pre- and post-intervention period of 14 weeks is chosen.

#### Statistical analysis

All data will be entered in MS Access 2007 and will be analyzed with IBM SPSS Statistics 24.

Patients from the intervention and control group will be compared for all baseline characteristics using *t*-test for continuous normally distributed variables, Mann-Whitney *U*-test for continuous non-normally distributed variables and chi square test for categorical variables.

For the primary outcome (MTEs) relative risks and 95% confidence intervals will be calculated. As the study has a pre- and post-design, results will be corrected for potential confounders by using multivariate logistic regression analysis.

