**Fig. 4 Fig4:**
[figure not shown]
Flow chart. Assessment of unintended medication discrepancies. BPMH = best possible medication history, ICU = intensive care unit, MTE = medication transfer error, PDMS = patient data monitoring system

The secondary outcome measure of this study is the proportion of patients with a potential adverse drug event (pADE) score due to an MTE, both at the moment of admission and at the moment of discharge. In addition, the pADEs scores and the associated costs are secondary outcome measures. A pADE score is defined as a potential and severity score for discomfort, harm and/or clinical deterioration caused by an unintentional discrepancy [19].

Determination of the potential and severity that a patient will experience harm due to an MTE will be based on the methodology described by Nesbit et al [19]. The same method was recently used by Gallagher et al [20]. This method uses the following categories for probability and severity of harm: 0 (zero; no harm expected by the MTE), 0.01 (very low: some harm is expected, but not clinically relevant), 0.1 (low: some harm is expected but poorly clinically relevant), 0.4 (medium; harm is expected, clinically relevant) or 0.6 (high; harm is expected, life threatening). In order to assign the probability and severity category for each MTE, we will present all MTEs at ICU admission or discharge to two assessors; one hospital pharmacist/clinical pharmacologist and one internist/clinical pharmacologist in training, who will, independently from each other, make a judgment based on clinical data of the patient. In case of differences between the judgments, the assessors will come together to reach consensus. If consensus cannot be reached, the case will be presented to a internist/clinical pharmacologist, who will make the final decision.

Next, our preliminary cost-effectiveness analysis will estimate the incremental costs per prevented MTE of the TIM compared to usual care, from the hospital’s perspective. Costs will comprise both the costs incurred by the reconciliation process and cost avoidance due to preventing MTEs and their pADEs.

The cost avoidance of the TIM program will be determined through summation of the individual pADE judgment scores of the MTEs and multiplying it by the cost of an ADE in the pre-intervention period compared to the post-intervention period.

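### As written, the avoided-cost formula has no per-patient scaling or covariate adjustment, and the logistic regression named cannot adjust a summed pADE score or a cost

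*Protocol article*

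**What the plan says.** Outcome measures names a binary secondary outcome: "The secondary outcome measure of this study is the proportion of patients with a potential adverse drug event (pADE) score due to an MTE". It then adds two that are not binary: "In addition, the pADEs scores and the associated costs are secondary outcome measures". The same section gives the calculation for avoided cost: "summation of the individual pADE judgment scores of the MTEs and multiplying it by the cost of an ADE", with the pre-intervention period compared with the post-intervention period. It mentions neither a denominator nor a covariate. The economic analysis is labelled preliminary, and avoided cost is one of its two cost components; the other is pharmacist labour.

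Statistical analysis first gives relative risks with 95% confidence intervals for the primary outcome. It then says that, because of the pre- and post-design, "results will be corrected for potential confounders by using multivariate logistic regression analysis". No other adjustment method is named.

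On the phases, Sample size says: "Therefore a pre- and post-intervention period of 14 weeks is chosen". Patient data lists the case-mix variables collected, including age, APACHE II, SAPS II, admission type and referring ward.

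**The concern.** The article's own reason for correcting results is that the phases are not randomised. That reason applies to cost as much as to medication transfer errors (MTEs), since both come from the same patients in the same two periods. The cost formula contains no correction, however, and the one tool named cannot be applied to it. A sum of scores of 0, 0.01, 0.1, 0.4 or 0.6 is not a yes/no outcome, and neither is an amount in euros.

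There is also a scaling problem. Each phase lasts a fixed number of weeks, so the two phases need not contain equal numbers of patients. A sum grows with the number of patients.

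If both sentences are followed as they stand, the MTE result is adjusted while the avoided cost carries any difference in patient numbers or case mix. Estimating cost-effectiveness is a stated aim, and the Discussion names managers and policy makers among the intended readers.

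**Working it through.** **Inputs from the article.** The expected proportion of patients with an MTE: "it was estimated that this proportion is 30% in our study". The design values behind the stated 133 patients: "With an estimated 50% reduction of errors due to the intervention, an alpha of 0.05 and a power of 0.80 the calculated sample size is". The phase size: "With an estimated mortality of 35%, in each measurement phase 205 patients should be included". The article gives no cost of an ADE, no score distribution and no expected cost result, so there is no stated cost figure to reproduce.

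**Sample size, for the phase size used below.** For 30% against 15%, two-sided alpha 0.05 (sidedness is not stated) and power 0.80, the pooled formula gives 120.5 per phase. The continuity correction gives 120.5/4 × (1 + √(1 + 4/(120.5 × 0.15)))² = 133.5, close to the stated 133. Then 133/0.65 = 204.6, so 205. This agrees with the article and has no bearing on the cost question.

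**What the formula measures.** Let N be the number of patients in a phase and m the mean summed score per patient. Assume one ADE cost for both periods, so that it cancels. The share of pre-phase cost shown as avoided is

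1 − (N_post/N_pre) × (m_post/m_pre).

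Both ratios can move for reasons unrelated to TIM.

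**Patient numbers alone.** With m equal, no TIM effect, and an assumed 205 patients against 185, the result is 1 − 185/205 = 9.8% avoided.

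**Error load alone, N equal.** Assume a post-phase load that differs by x for reasons unrelated to TIM, with x from 5% to 20%. This range is an assumption; nothing in the documents supports a particular value.

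| Situation | Formula | Shown as avoided |
|---|---|---|
| No TIM effect, load lower by x | x | 5% to 20% |
| No TIM effect, load higher by x | −x | −5% to −20% |
| True 50% effect, load lower by x | 1 − 0.5(1 − x) | 52.5% to 60% |
| True 50% effect, load higher by x | 1 − 0.5(1 + x) | 47.5% to 40% |

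**A case-mix example tied to the 30%.** Assume high-risk patients have a 45% MTE risk and a mean score of 0.2 when an MTE occurs, and low-risk patients 15% and 0.1. A half-and-half mix gives 0.5 × 45% + 0.5 × 15% = 30%. With 205 patients per phase, no TIM effect and a high-risk share h, the summed score is 205 × (h × 0.09 + (1 − h) × 0.015).

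| h | Patients with an MTE | Summed score | Shown as avoided against h = 50% |
|---|---|---|---|
| 50% | 30% | 10.76 | 0% |
| 40% | 27% | 9.23 | 14% |
| 30% | 24% | 7.69 | 29% |
| 60% | 33% | 12.30 | −14% |

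Standardised to the pre-phase mix, avoidance is 0 in every row. The percentages do not depend on 205. A logistic model that included the risk group would remove the shift from the MTE column. Nothing named in the article would remove it from the summed score.

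**The case against.** The strongest reply is that this is a silence and not an error. Outcome measures defines what is counted and how it is valued; it defines the primary outcome without covariates too, and adjustment appears only later. The correction sentence directly follows the one on the primary outcome and most naturally refers to it, where logistic regression is suitable. The model for a preliminary economic analysis could be left to a full protocol or analysis plan that is not shown. Baseline characteristics will be compared between phases, so a measured shift would be visible, and the Discussion concedes that the design is weaker.

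Much of this stands. A reader might infer that the plan commits to an unadjusted cost comparison, or wrongly assigns logistic regression to costs. The text says neither. A reader might also infer that a case-mix shift will be reported as savings. The documents show no shift, and the bias could run either way. Nor would an unchanged MTE proportion beside a lower cost prove a fault: the primary outcome counts patients with any MTE, whereas cost weights each MTE, so fewer or milder errors per affected patient could lower cost alone.

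What the reply does not remove is that the article states an explicit between-period calculation, and that the only correction it names cannot be applied to that calculation. A table of baseline differences does not adjust a cost.

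**Conclusion.** The point holds in limited form. It covers the summed pADE scores and the avoided cost derived from them. It does not cover the proportion of patients with a pADE, which logistic regression can handle. Followed as written, the formula passes differences in patient numbers and case mix between two calendar-defined, non-randomised phases directly into the avoided cost, upwards or downwards.

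The size cannot be estimated from the documents. The 5% to 20% range and the 14% and 29% in the example show the mechanism under assumed inputs and do not predict a bias. The formula is worth correcting before analysis, but this is a preliminary secondary result and the primary comparison is unaffected.

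**What to change.** Replace the period totals with a per-patient analysis:

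- Compute the summed pADE score and resulting cost for every included patient, with 0 for patients without an MTE.
- Estimate the difference between phases with the same confounders as the primary analysis, by a regression for a mean or by regression standardisation.
- Give a bootstrap confidence interval that resamples patients, which also respects the inclusion of ICU readmissions.
- Base avoided cost on the adjusted per-patient difference, and show the crude figure beside it.
- State that the logistic regression is for the binary outcomes.

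The variables under Patient data are already to be collected, so no new data are needed. The cost is some wording and programming, and the adjusted saving may prove less favourable or less precise than the crude one. Adjustment covers measured differences only; unmeasured changes over time between the phases would remain.
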